#### Secondary outcomes

The following secondary outcomes will reported: (1) the number and length of delirium episodes during hospital stay and the number of days between admission to ward and the occurrence of delirium and (2) the outcome of the patient-reported questionnaires.

The number of deaths, the number of eligibility violations and the number of participants who fall during their hospital stays will also be reported overall and by arm. The type of living accommodation at 3 months will be compared with that at baseline and intended discharge location.

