## Methods/Design

### Aims and objectives

We aim to conduct a pragmatic, multicentre, cluster randomised, controlled feasibility study to explore the potential effectiveness and cost-effectiveness of the POD system of care versus standard care practice in older patients at risk of developing delirium who are admitted to hospital for emergency care. The study objectives relate to gathering data to inform the feasibility of conducting a definitive RCT. The primary objectives are toProvide a preliminary estimate of the effectiveness of POD compared with standard care as measured by the incidence of new-onset delirium within 10 days of hospital admission (anticipated primary outcome for a definitive trial)Assess the variability of the incidence of new-onset delirium within 10 days of hospital admission in both treatment groupsEstimate the intracluster correlation coefficient and likely cluster sizeAssess barriers to the delivery of the POD system of careAssess compliance with the POD system of careEstimate recruitment and follow-up rates at both patient and cluster levelsAssess the degree of contamination at ward level due to between-ward staff movementsInvestigate differences in financial costs and benefits between the POD system of care and standard practice

Our secondary objectives are to investigate differences in the number, severity and length of delirium episodes (including persistent delirium); length of stay in hospital; in-hospital mortality; destination at discharge; health-related quality of life and health resource use; physical and social independence; anxiety and depression; and patient experience.

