### Data collection

The screening data will be obtained by the RA in consultation with the attending ward staff and will include demographic characteristics, admission details and, where applicable, assessment of capacity and a delirium screen and/or CAM severity rating (CAM-S) [43, 45] for all patients older than 65 years of age admitted to the ward. Baseline assessment will be conducted by the RA and will include admission details, reason for admission, medical history (including the Charlson comorbidity index) [51], existing hearing and or visual impairments, current medication use, illness severity (using an early warning score [National Early Warning Score or equivalent]), CAM-S), cognitive assessment (history of dementia and Abbreviated Mental Test Score) [46], medications and living arrangements. Participants will complete questionnaires relating to physical and social independence (Nottingham Extended Activities of Daily Living Scale) [52] and health-related quality of life (EuroQol [EQ-5D]) [53]. The RA will perform daily cognitive and CAM assessments for up to 10 days postadmission (or until discharge, whichever is sooner) to detect the incidence of new delirium.

At 30 days after admission to the ward, the RA will perform a cognitive assessment and CAM and ask the patient to complete questionnaires about health-related quality of life (EQ-5D) [53], anxiety and depression (using the Clinical Anxiety Scale [54] and the Geriatric Depression Scale Short Form [55], respectively) and about patient experience using selected questions in the patient-reported experience measure from the National Audit of Intermediate Care [56]. At the point of discharge, the RAs will collect data on the date of discharge (or date of death), causes of death (if known), falls occurring (and reason for fall if known) between the date of consent and date of discharge using local recording procedures (e.g., falls incidence records) and discharge destination.

At 3 months after admission to the ward, postal questionnaires will be used to provide information on physical and social independence (Nottingham Extended Activities of Daily Living Scale) [52], health-related quality of life (EQ-5D) [53], health care resource use (post discharge contact with health and social care services) and information on living arrangements. Proxy completion of the questionnaires and the resource use will be permitted.

A summary of the assessments to be used is given in Table 2.

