**Table 2 Tab2:** Summary and timing of assessments

Assessment	Screening/recruitment	Baseline	Daily (up to 10 days from date of admission)	30 days (postadmission)	Discharge	Follow-up (3 mo postadmission)
Demographic data (age, sex, ethnicity)	X					
Admission details (date and time of admission to hospital and ward)	X					
Assessment of capacity	X					
Delirium screen (confusion assessment method) and delirium severity rating (CAM-S)	X		X	X		
Date of discharge and discharge destination (living alone, living with another person, nursing home, residential care home or other)					X	
Reason for admission (hip fracture, other orthopaedic condition, medical condition) and medical history (Charlson comorbidity index, existing hearing and/or visual impairments, current medication use [benzodiazepines, opiates, H_1_ antihistamines])		X				
Cognitive impairment: (1) history of dementia, (2) low Abbreviated Mental Test Score on admission		X				
Illness severity using National Early Warning Score or equivalent		X				
Living arrangements (living alone, living with another person, nursing home, residential care home or other)		X			X	X
Nottingham Extended Activities of Daily Living Scale^a^		X				X
EuroQol EQ-5D^a^		X		X		X
Geriatric Depression Scale Short Form^a^				X		
Clinical Anxiety Scale				X		
Patient-reported experience measure				X		
Falls (and reason for fall if known)	Occurring between the date of consent and date of discharge					
Health care resource use (postdischarge contact with health and social care services)^a^						X

*Abbreviation: CAM-S* confusion assessment method severity rating

^a^Proxy completion permitted where appropriate

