### Sample size

We aim to recruit 720 patients into this feasibility study. This is based on the following assumptions:Average length of stay of 14 days and 25-bed wards will provide a recruitment pool of 4800 patients over the course of 6 months.Fifty percent of patients are assumed to be at risk of delirium, giving 2400 eligible patients.On the basis of previous studies of comparable populations [58, 59], 30 % of patients will consent.

Because this is a feasibility study, a formal power calculation is not appropriate, as effectiveness is not being evaluated. The results generated from this study will be used to inform the power calculation for a possible definitive study.

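### Number and length of delirium episodes are to be reported for the whole hospital stay, but daily CAM ends at day 10, so both are understated for patients who stay longer

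*Protocol article*

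**What the plan says.** - **Outcome.** In the protocol article, Analysis, Secondary outcomes, the plan will report "the number and length of delirium episodes during hospital stay". The matching secondary objective, under Aims and objectives, is to investigate differences in the "number, severity and length of delirium episodes (including persistent delirium").
- **Daily assessment.** Under Data collection, the research assistant does "daily cognitive and CAM assessments for up to 10 days postadmission (or until discharge, whichever is sooner"). The column heading in Table 2 agrees: "Daily (up to 10 days from date of admission").
- **Later assessment.** There is one: "At 30 days after admission to the ward, the RA will perform a cognitive assessment and CAM".
- **Discharge.** "At the point of discharge, the RAs will collect data on the date of discharge (or date of death"), with cause of death, falls and destination. No CAM is listed there, and the Discharge column of Table 2 has no CAM entry.
- **Length of stay.** The Sample size section assumes "Average length of stay of 14 days and 25-bed wards".

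**The concern.** The outcome is defined over one window and observed over a shorter one. The two agree for a patient discharged by day 10. For a patient who stays longer they do not:

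- An episode that starts after day 10 is not counted. The single day-30 CAM may find delirium present, but it cannot say when an episode began or how many there were.
- An episode still open at the last daily CAM has no known end, so its recorded length is a minimum. One that starts on day 8 can record at most 3 days (days 8, 9 and 10), however long it lasts.

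Reported as outcomes of the hospital stay, both quantities come out too low. They serve a secondary objective framed as differences between arms, and the study exists to inform a definitive trial. Figures labelled as covering the stay would carry the error into that design.

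**Working it through.** **1. Is 14 days a figure the plan relies on?** Inputs: 16 wards (Setting); 25 beds, 14-day mean stay, 50% at risk and 30% consent (Sample size). Taking 6 months as 24 weeks, or 168 days:

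- Pool = 16 × 25 × (168 / 14) = 4800, as stated.
- Eligible = 4800 × 0.50 = 2400, as stated.
- Target = 2400 × 0.30 = 720, as stated.

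So the 14-day mean drives the recruitment target. With 182 days the pool would be 5200, so 24 weeks is evidently what was used.

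**2. Smallest share of inpatient days without a daily CAM.** Let L be length of stay with mean 14. Days after day 10 average E[max(L − 10, 0)], which cannot be less than 14 − 10 = 4. The share is therefore at least 4/14 = 0.286, or 29%. A set of stays all equal to 14 days attains this minimum. It needs the mean only, with no assumption on shape.

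**3. Share under assumed shapes.** The documents give no distribution, so these rows are assumptions, all with mean 14 days.

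- Exponential: P(L > 10) = exp(−10/14) = 0.490. The share of days after day 10 is the same, 0.490.
- Exponential shifted to a 2-day minimum: P(L > 10) = exp(−8/12) = 0.513. Share of days = 12 × 0.513 / 14 = 0.440.
- Others, by numerical integration of the survival function beyond day 10, divided by 14:

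| Assumed stay (mean 14 d) | Patients beyond day 10 | Days beyond day 10 |
|---|---|---|
| Exponential | 49% | 49% |
| Shifted exponential, minimum 2 d | 51% | 44% |
| Gamma, shape 2 | 58% | 41% |
| Gamma, shape 4 | 68% | 35% |
| Lognormal, sigma 1 | 44% | 49% |
| Lognormal, sigma 0.7 | 55% | 40% |
| Lognormal, sigma 0.5 | 66% | 35% |

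Of 720 participants, about 313 to 489 would stay beyond day 10 under these shapes.

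**4. Can the day-30 CAM close the gap?** For the unshifted shapes above, between 3% and 12% of patients would still be in hospital at day 30. For the rest, that CAM falls after the stay has ended. For all of them it is one point in time and cannot date or count episodes between days 11 and 30.

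**5. Are open episodes likely?** The Background cites a systematic review in which delirium persisted in 45% of cases at discharge and 33% at 1 month. If that is roughly right here, a lower-bound length will not be rare.

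**The case against.** The strongest defence is that this is a feasibility study. Its analysis is descriptive, its anticipated primary outcome is limited to 10 days by design, and detail is left to a statistical analysis plan. The article does not say that recorded days will be taken as full episode length, and how an episode is defined or censored properly belongs in that plan. Much of this stands. The 10-day incidence outcome matches the daily CAM and is untouched, and no progression criterion uses episode number or length. But an analysis plan cannot recover assessments that were never scheduled, and the article itself fixes the window as the hospital stay. The case-note review under Data collection is for compliance and is not named as a source of delirium data.

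Four stronger readings are tempting, and the documents do not support them:

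- **That CAM stops altogether at day 10.** Only the daily CAM stops; a further CAM is planned at day 30. For patients discharged by day 10 the outcome can be measured as stated.
- **That persistent delirium cannot be assessed.** Nothing says it will be taken from the daily data, and the day-30 CAM can supply it.
- **That the cut-off would imitate a benefit if POD shortens stay.** The cut removes days only from patients still in hospital. With shorter POD stays, control patients would have more unobserved days, which would tend to hide a benefit. Discharge also ends an outcome defined on the stay, so it is not truncation of that outcome.
- **That about half of all episodes are lost.** The 44% to 49% figures are shares of inpatient days under an assumed distribution. Equating days with episodes needs onset to be uniform over the stay, which the documents do not support.

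**Conclusion.** The point holds as a mismatch between the stated outcome and the assessment schedule. For patients in hospital beyond day 10, the number and length of episodes over the stay cannot be obtained from the planned data and will be understated.

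The firm size is that at least 29% of inpatient days have no daily CAM, given a mean stay of 14 days. Anything above that depends on the assumed shape. The 14 days is a planning figure for all admissions. Excluding patients with discharge planned within 48 hours would tend to lengthen participants' stays and so raise the share. The proportion of episodes missed or cut short cannot be calculated from the documents.

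The direction of any bias between arms is uncertain. One route is plausible: if POD delays onset, episodes move towards or past day 10 and could look fewer or shorter. The severity part of the objective has the same limit, because CAM-S follows the CAM schedule.

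**What to change.** Reconcile the Secondary outcomes section with Data collection and Table 2:

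1. Restate the outcome as the number of delirium episodes and of CAM-positive days within the first 10 days after admission, each per assessed day.
2. Analyse episode length as right-censored when the patient is still CAM-positive at the last daily CAM. Show how many episodes are censored in each arm, and how many of those at day 10 and at discharge.
3. Report delirium at the day-30 CAM separately, as the measure of persistence.

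The Trial status section says follow-up has ended and analysis is under way, so the remedy has to be in wording and method. It needs no new data. The cost is a narrower claim: the results describe the first 10 days and not the whole hospital stay.

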### Intervention

POD is a manualised, multicomponent intervention and systematic implementation process designed to secure ward practice changes, potentially enhanced by the involvement of hospital volunteers. It builds on current best evidence on delirium prevention [3], conceptually driven empirical research [48] and reviews of implementation [29, 49, 50].

The POD intervention comprises actions centred on 10 targeted risk factors associated with the development of delirium among those who are vulnerable on of the basis of predisposing risk [3]. These interventions directly affect the patient experience of care and include optimising hydration and nutrition, reducing environmental threats (excessive noise, multiple moves), increasing orientation to time and place, improving communicative practices (personally meaningful interaction and cognitive stimulation), supporting and/or encouraging mobility and better management of pain and infection. The implementation process is supported and reinforced through raising awareness and training of staff and volunteers in delirium prevention. Alongside this, staff will be involved in an action-planning cycle of observation and audit of current practice to establish what needs to be put in place to introduce the POD system of care. The principles underpinning POD and the steps in the change process to facilitate action on the intervention are standard and generalisable, although the specific systems or mechanisms are flexible, depending on preexisting practice and local decision-making.

Wards randomised to the POD system of care will undergo a 6-month implementation period to allow the intervention to be embedded into ward practice before patient recruitment. Local implementation teams, including a study-specific ward nurse, will be convened, and training will be provided in the implementation and delivery of the POD system of care by the central trial team. Progress on implementation will be monitored by the central trial team through regular site visits and telephone and/or email contact and will be tracked through completion of an internal milestone checklist embedded within the POD manual.

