### Recruitment and consent

Following a 6-month implementation period for the POD intervention, study participants will be recruited over a 6-month period. All patients 65 years of age or older admitted to a participating ward will be considered for enrolment into the study in a three-stage recruitment process:Initial screening for eligibility will be established through a liaison between the RA and the ward staff (stage 1).Patients will be screened for the presence of delirium by the RA within 24 hours of admission to the ward (e.g., elderly care patients) or preoperatively (e.g., hip fracture patients) (stage 2).Patients who do not have prevalent delirium will then be invited by the RA to participate in the trial within 48 hours of admission to the ward. The RA will obtain informed consent from the participant or, if the patient lacks the capacity to provide consent, from a personal or nominated consultee (stage 3).

Figure 2 provides an overview of the recruitment process.

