Compliance with the POD system of care will be assessed by the central trial team through review of site-specific POD documentation, case note review and researcher-conducted observations of ward care using the method employed in the 2013 National Audit of Dementia Care in General Hospitals [57]. Sustainability will be assessed through observations of ward care approximately 3–6 months post recruitment through central trial team researcher-conducted observations of ward care. Information will be collected on intervention delivery, recruitment uptake, follow-up rates, missing data, length of hospital stay, staff movement (to allow for an assessment of potential contamination), the number of falls between consent and discharge, and deaths occurring up to 3 months post admission. We will also collect related and unexpected serious adverse events.

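### The falls summary is labelled as covering the hospital stay although falls are collected only from consent to discharge, and it counts fallers with no total of falls and no time denominator

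*Protocol article*

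**What the plan says.** The article describes falls in four places.

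- **Data collection, text on discharge data.** Research assistants record "falls occurring (and reason for fall if known) between the date of consent and date of discharge using local recording procedures".
- **Table 2, falls row.** The timing is given as "Occurring between the date of consent and date of discharge".
- **Data collection, closing paragraph.** The information to be gathered includes "the number of falls between consent and discharge, and deaths occurring up to 3 months post admission". The unit here is a count of events.
- **Analysis, Secondary outcomes.** The result to be reported is "the number of participants who fall during their hospital stays will also be reported overall and by arm". The unit here is a count of people, and the period is the hospital stay.

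Three other statements bear on the point. Recruitment and consent says that patients without delirium are "invited by the RA to participate in the trial within 48 hours of admission to the ward". Aims and objectives lists length of stay among the outcomes to be compared, and Data collection gathers it. The Intervention section includes "supporting and/or encouraging mobility and better management of pain and infection" among the care components.

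**The concern.** The reported quantity and the collected quantity differ in two ways, and the reported one lacks a third element.

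1. **Window.** The hospital stay starts before consent. Falls between admission and consent are not in the data, so a table headed with the hospital stay would claim more coverage than it has.
2. **Unit.** Falls are counted, but only people who fall are listed for reporting. A participant with three falls contributes the same as one with a single fall.
3. **Exposure.** Observation ends at discharge. If one arm has shorter stays, its participants have fewer days in which to be seen falling.

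Falls matter here because they could move in either direction. The intervention encourages mobility, and the Background section lists falls among the consequences associated with delirium. Deaths and falls are the only clinical harms that the Secondary outcomes section names for reporting by arm. Readers, and those planning the definitive trial, will compare the arms on this line even without a formal test.

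**Working it through.** **The plan's own figures.** The article gives no fall rate and no expected number of falls. The figures used from Sample size are the 14-day average stay and the target of 720. The target reproduces: 16 wards × 25 beds × (168 days ÷ 14 days) = 4800; × 0.50 = 2400; × 0.30 = 720. An equal split, assumed here, is 360 per arm.

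**Step 1: the window.** With consent at the 48-hour limit, the uncounted ward time is at most 2 ÷ 14 = 14.3% of the average stay. With consent at 24 hours it is 1 ÷ 14 = 7.1%. Hospital time before the ward comes on top.

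**Step 2: fallers under an equal daily rate.** Assume a constant daily rate r, a fixed number of observed days d, and Poisson falls. Then P(at least one fall) = 1 − exp(−r × d). Assume r = 0.006 (6 per 1000 patient-days). Compare stays of 14 and 12 days with consent at 48 hours, which leaves 12 and 10 observed days.

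- 12 days: 1 − exp(−0.072) = 0.0695, or 360 × 0.0695 = 25.0 fallers.
- 10 days: 1 − exp(−0.060) = 0.0582, or 360 × 0.0582 = 21.0 fallers.
- Ratio: 0.0582 ÷ 0.0695 = 0.84.
- Ratio of falls per patient-day: 0.006 ÷ 0.006 = 1.00.

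**Step 3: the reverse case.** If the arm with 10 observed days has a 20% higher rate (0.0072), then 1 − exp(−0.072) = 0.0695. The faller proportions are equal and the excess does not show. The cancellation is exact because 12 ÷ 10 = 1.2, so this shows the mechanism and is not a prediction.

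**Step 4: sensitivity to the assumptions.**

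| Assumed falls per 1000 patient-days | Faller ratio, 12- v 14-day stay | Faller ratio, 10- v 14-day stay |
|---|---|---|
| 3 | 0.836 | 0.671 |
| 6 | 0.838 | 0.675 |
| 9 | 0.841 | 0.679 |
| 12 | 0.843 | 0.683 |

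The ratio hardly depends on the fall rate. It depends on the difference in stay, which is assumed.

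**Step 5: repeat falls left out of the summary.** Per arm of 360 over 12 observed days, the number is 360 × [r × d − (1 − exp(−r × d))]. At r = 0.006 this is 360 × (0.0720 − 0.0695) ≈ 0.9. Over 3 to 12 per 1000 it runs from 0.2 to 3.6. It would be larger if falls cluster within patients.

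**The case against.** The best defence is that the article defines the window the same way three times, and that the Secondary outcomes sentence is a loose one-line summary of it. The sentence counts participants, and nobody is a participant before consent, which the Recruitment and retention section says is for provision of data only. Starting collection at consent is a normal limit. This stands: the fault lies in the label and not in the start date.

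A reader might infer that repeat falls are lost. They are not, because the article collects "the number of falls between consent and discharge"; they are only absent from the listed summary. A reader might also infer that the choice of reporting measure loses the early falls. It does not. They are absent because collection starts at consent, and rewording recovers none of them.

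A further defence is that a rate per patient-day is a detail that the analysis plan can add, and that fall counts, discharge or death dates and length of stay already allow it. That is fair as far as the rate is concerned. But the article does not leave the measure open: it states a unit, a period and a split by arm, and the unit and period do not match what is collected.

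Cumulative fallers per participant is also a legitimate measure if a shorter stay is part of the intervention's effect. A daily rate is not neutral either when risk varies over the stay. This stands, and it argues for showing both measures.

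Lastly, the shift in the illustration is small against the noise. For 6.9% versus 5.8% with 360 per arm, the 95% half-width is 1.96 × √(0.0695 × 0.9305 ÷ 360 + 0.0582 × 0.9418 ÷ 360) ≈ 3.6 percentage points before any allowance for clustering, against a shift of 1.1 points.

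**Conclusion.** The point holds as a minor one. The period named in Secondary outcomes is wider than the period of collection, by up to 48 hours of ward time (at most 14% of the planned average stay) plus any earlier hospital time. The listed measure omits repeat falls that are collected. It also has no exposure denominator, so under an equal daily rate the faller ratio would be about 0.84 for a 12- versus 14-day stay and about 0.67 to 0.68 for a 10- versus 14-day stay. Those ratios rest on assumed stays, a constant rate and consent at 48 hours. The documents give no fall rate and no expected difference in stay.

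It might be inferred that the safety comparison between arms is distorted by any change in length of stay. The documents do not support that. Falls are not among the stated objectives, the Analysis section puts description and confidence intervals ahead of formal testing, and safety oversight rests with the steering committee. Neither progression guideline uses falls. The accurate statement is that the count can differ between arms for reasons of exposure alone, and that the listed summary would not show this.

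**What to change.** In Secondary outcomes, remove the reference to the hospital stay and state the falls result along these lines: *for the window from consent to discharge or death, by arm and overall, the number of participants with at least one fall, the total number of falls, and falls per 1000 patient-days.*

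No new data are needed. Fall counts and dates of discharge or death are already collected, and the date of consent already defines the window. The cost is one reworded sentence and one extra table row. The small downside is that the reported window is openly narrower than the hospital stay.
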